## Abstract

**Background:**

Standard lifestyle interventions have shown limited efficacy in preventing type 2 diabetes among individuals with isolated impaired fasting glucose (i-IFG). Hence, tailored intervention approaches are necessary for this high-risk group.

**Objective:**

This study aims to (1) assess the feasibility of conducting a high-intensity interval training (HIIT) study and the intervention acceptability among individuals with i-IFG, and (2) investigate the preliminary efficacy of HIIT in reducing fasting plasma glucose levels and addressing the underlying pathophysiology of i-IFG.

**Methods:**

This study is a 1:1 proof-of-concept randomized controlled trial involving 34 physically inactive individuals (aged 35-65 years) who are overweight or obese and have i-IFG. Individuals will undergo a 3-step screening procedure to determine their eligibility: step 1 involves obtaining clinical information from electronic health records, step 2 consists of completing questionnaires, and step 3 includes blood tests. All participants will be fitted with continuous glucose monitoring devices for approximately 80 days, including 10 days prior to the intervention, the 8-week intervention period, and 10 days following the intervention. Intervention participants will engage in supervised HIIT sessions using stationary “spin” cycle ergometers in groups of 5 or fewer. The intervention will take place 3 times a week for 8 weeks at the Aerobic Exercise Laboratory in the Rehabilitation Hospital at Emory University. Control participants will be instructed to refrain from engaging in intense physical activities during the study period. All participants will receive instructions to maintain a eucaloric diet throughout the study. Baseline and 8-week assessments will include measurements of weight, blood pressure, body composition, waist and hip circumferences, as well as levels of fasting plasma glucose, 2-hour plasma glucose, and fasting insulin. Primary outcomes include feasibility parameters, intervention acceptability, and participants’ experiences, perceptions, and satisfaction with the HIIT intervention, as well as facilitators and barriers to participation. Secondary outcomes comprise between-group differences in changes in clinical measures and continuous glucose monitoring metrics from baseline to 8 weeks. Quantitative data analysis will include descriptive statistics, correlation, and regression analyses. Qualitative data will be analyzed using framework-driven and thematic analyses.

**Results:**

Recruitment for the study is scheduled to begin in February 2025, with follow-up expected to be completed by the end of September 2025. We plan to publish the study findings by the end of 2025.

**Conclusions:**

The study findings are expected to guide the design and execution of an adequately powered randomized controlled trial for evaluating HIIT efficacy in preventing type 2 diabetes among individuals with i-IFG.

**Trial Registration:**

Clinicaltrials.gov NCT06143345; https://clinicaltrials.gov/study/NCT06143345

**International Registered Report Identifier (IRRID):**

PRR1-10.2196/59842

## Introduction

The prevalence of type 2 diabetes is increasing globally [1-3], driven predominantly by a rising number of individuals with prediabetes [2]. Globally, an estimated 860 million (8.4%) adults are living with prediabetes, a condition that increases the risk of developing type 2 diabetes [2], micro- and macrovascular complications, and mortality [4].

Prediabetes is not a singular entity but rather a heterogeneous group of metabolic defects that often precede type 2 diabetes [5-7]. Prediabetes phenotypes include isolated impaired fasting glucose (i-IFG), isolated impaired glucose tolerance (i-IGT), and IFG + IGT. Each prediabetes phenotype exhibits distinct pathophysiological abnormalities [5-7]. i-IFG is marked by impaired early-phase insulin secretion and hepatic insulin resistance. Conversely, i-IGT involves impairments in both early- and late-phase insulin secretion and skeletal muscle insulin resistance [5,7]. IFG + IGT presents a combination of defects observed in both i-IFG and i-IGT [5,7]. i-IFG accounts for a substantial portion of the global prediabetes population, ranging from 43.9% to 58% among Caucasian individuals and 29.2% to 48.1% among Asian individuals, depending on the diagnostic criteria [8]. Individuals with i-IFG exhibit a 4 to 5.5 times higher rate of progression to type 2 diabetes, depending on the diagnostic criteria, compared to those with normoglycemia [9].

Individuals with prediabetes are typically advised to adopt standard lifestyle interventions that emphasize improving diet quality with a modest calorie restriction and increasing moderate-intensity physical activity to reduce the risk of developing type 2 diabetes [10,11]. However, recent research highlights the varied effectiveness of these interventions among different prediabetes phenotypes. While these approaches prove highly effective for individuals with i-IGT and IFG plus IGT, their efficacy is notably limited for those with i-IFG [6,12,13]. Thus, there arises a necessity for alternative lifestyle intervention strategies tailored specifically to individuals with i-IFG.

One of the promising approaches is high-intensity interval training (HIIT), recognized as a time-efficient exercise option with significant benefits for metabolic health [14]. HIIT entails alternating short bursts of high-intensity exercise with periods of less active or passive recovery [15]. It is noteworthy that HIIT represents a more intensive exercise regimen compared to the current physical activity recommendations for individuals with prediabetes [10,11].

HIIT has been shown to effectively reduce hepatic insulin resistance and improve early-phase insulin secretion in individuals with type 2 diabetes [16-20], leading to significant reductions in fasting plasma glucose (FPG) levels [17,21-25]. Given that i-IFG shares these same pathophysiological defects [5-7], it is reasonable to hypothesize that HIIT could also be effective in individuals with i-IFG, as depicted in Figure 1. However, this hypothesis has yet to be tested in a randomized controlled trial (RCT). This is a critical investigation, as reducing fasting hyperglycemia is key to preventing the progression of type 2 diabetes in those with i-IFG [6,26]. To inform the design and implementation of this RCT, we propose conducting a proof-of-concept study among individuals with i-IFG, with the following objectives.

Primary objectives (feasibility and acceptability): (1) assess the feasibility of recruiting and retaining participants and executing study procedures; (2) examine the feasibility, acceptability, and appropriateness of the HIIT intervention for participants; and (3) investigate participants’ experiences, perceptions, and satisfaction with the HIIT intervention, and identify facilitators and barriers to participation.Secondary objective (preliminary efficacy): Investigate the preliminary efficacy of HIIT in reducing FPG levels and addressing the underlying pathophysiology of i-IFG.

**Figure 1 figure1:**
[figure not shown]
Potential pathways through which high-intensity interval training sessions may address the pathophysiological abnormalities and fasting hyperglycemia in individuals with isolated impaired fasting glucose. VLDL: very low-density lipoprotein.

## Methods

### Study Design, Study Setting, and Participants

The study will be reported in accordance with the CONSORT (Consolidated Standards of Reporting Trials) guidelines for randomized pilot and feasibility trials [27]. This is a “proof-of-concept” 1:1 parallel-group RCT involving 34 physically inactive individuals aged 35-65 years who are overweight or obese and have i-IFG. Figure 2 presents the study’s CONSORT diagram. The Georgia Clinical Research Center (GCRC) at Emory University Hospital will serve as the site for participant recruitment and conducting study procedures. A highly trained and experienced study coordinator will recruit participants through a comprehensive 3-step screening procedure.

**Figure 2 figure2:**
[figure not shown]
CONSORT (Consolidated Standards of Reporting Trials) flow diagram. CGM: continuous glucose monitoring; HIIT: high-intensity interval training; i-IFG: isolated impaired fasting glucose; OGTT: oral glucose tolerance test; REDCap: Research Electronic Data Capture.

### Step 1: Screening (via Electronic Health Records)

Potential participants will be identified using Emory’s electronic health care records system, known as “MyChart.” Queries within this database will target individuals aged 35-65 years with a BMI≥25 kg/m^2^ (≥23 kg/m^2^ if Asian descent) [28], who have been diagnosed with prediabetes (hemoglobin A_1c_ [HbA_1c_] 5.7%-6.4%) [29] within the last 12 months, have no diagnosis of diabetes (FPG≥126 mg/dL or 2-hour plasma glucose ≥200 mg/dL or HbA_1c_≥6.5% or currently taking antidiabetic drugs) [29], not currently taking weight-loss medications, not currently taking drugs known to influence glucose tolerance (steroids and antipsychotics), not currently taking beta-blockers and calcium channel blockers (individuals taking these drugs will not reach heart rate (HR) targets for the HIIT sessions), did not undergo bariatric surgery, no anemia (anemia may limit the exercising capacity), and have no chronic illnesses (cardiovascular disease, stroke, cancers, chronic respiratory diseases, and mental health disorders). Individuals meeting these criteria will receive an invitation through the MyChart platform to participate in the second screening step.

### Step 2: Screening (via Phone Calls)

Those expressing interest in participating in the study through MyChart will be contacted via phone. During these calls, individuals will receive a comprehensive explanation of the study and have any questions addressed. They will then be asked to sign an electronic consent form via Emory’s REDCap (Research Electronic Data Capture; Vanderbilt University) platform [30]. Following consent, potential participants will complete a questionnaire to assess their eligibility for step 3 screening based on the following criteria.

Physically inactive (less than 150 minutes per week of moderate-intensity physical activity, less than 75 minutes per week of vigorous-intensity physical activity, and <600 metabolic equivalent task–minutes per week) [31] assessed by the International Physical Activity Questionnaire (IPAQ) [32].Available to participate in the HIIT group sessions.No history of smoking (smoking is associated with reduced insulin secretion and increased insulin resistance) [33].Not enrolled in weight loss programs in the past 6 months.Not enrolled in any regular exercise programs in the past 6 months.Not currently following a specific diet (eg, ketogenic and Mediterranean).No plans to undergo bariatric surgery during the study period.No plans to relocate outside the study area during the study period.Not pregnant.Not breastfeeding.

### Step 3: Screening (via In-Person Clinic Visits)

Individuals meeting the step 2 criteria will be invited to visit the GCRC at Emory University Hospital after fasting overnight for a minimum of 8 hours [29]. During the visit, participants will complete standard questionnaires to collect sociodemographic information (education, occupation, and marital status) [34,35] and details on alcohol consumption [34,35] and dietary intake [36]. Additionally, physical measurements will be conducted using standardized instruments in accordance with the World Health Organization’s STEPwise approach to noncommunicable disease risk factor surveillance (STEPS) protocol [37]. Following these assessments, individuals will undergo an oral glucose tolerance test (OGTT) and provide blood samples for insulin. Individuals diagnosed with i-IFG, defined by the American Diabetes Association criteria as FPG between 100-125 mg/dL and 2-hour plasma glucose<140 mg/dL [29], will be deemed eligible to participate in the study. Individuals without i-IFG will be excluded from further participation in the study. They will receive a summary report of their test results and general healthy lifestyle advice and will be referred to their general practitioner if they have IGT or undiagnosed diabetes for further management.

### Randomization and Blinding

Participants will be equally randomized into either the intervention or control group after completing baseline assessments and being found eligible, using a computer-generated randomization sequence by a statistician not involved in the trial. Given the nature of the study, only specific personnel such as nursing staff, laboratory personnel, and the data analyst will be blinded to participant allocation to the study groups. Participants, the study coordinator, the HIIT intervention instructor, and the principal investigator will not be blinded to participation allocation.

### Intervention

Following the recommendation of the American College of Sports Medicine [38], participants in the intervention group will be required to obtain medical clearance from their general practitioner before starting the HIIT sessions. These sessions, led by a qualified exercise physiologist (the instructor) and adhering to standard protocols [39,40], will take place in the Aerobic Exercise Laboratory at Emory University's Rehabilitation Hospital. Using “spin cycle ergometers” (Schwinn), sessions will be conducted in small groups of 5 or fewer participants at specified times on Mondays, Wednesdays, and Fridays, spanning 8 weeks. Each participant will undergo a maximum of 24 HIIT sessions. Each session will consist of a 5-minute warm-up, followed by an interval-based workout phase with steady up-tempo cadences, sprints, climbs, and interspersed recovery periods. A 5-minute cooldown will conclude each session. The workout sessions will initially last 20 minutes and will progressively increase in time based on participants’ tolerance and instructor recommendations. Each session will include “active rest” periods where resistance is reduced to lower HR, alternating with high-intensity intervals featuring sprints or climbs to elevate HR. The duration of active rest versus high-intensity intervals will be adjusted according to individual responses and target HR. To monitor and maintain intensity within the target HR range, participants will wear Polar H10 chest strap HR sensors [41]. The target HR will be calculated using the Karvonen method [42]. Exercise intensity will begin at 75% of the estimated maximum HR reserve (HRR) and will increase by 5% every week, as tolerated or deemed necessary by the instructor, over the 8-week intervention period. During the workout phase, the target HRR reserve will be maintained by averaging increases and decreases in intensity or HR with a target to maintain within a 10% offset from the HRR goal [39,40]. Participants will need to adhere to within-session HR targets at an 80% rate (or greater) for a session to be counted as attended and participants will need to attend 19 out of 24 sessions to be included as a “completer” in the final data analysis. To date, our interventions have yielded a within-session adherence rate to the prescribed intervention of 91% (as measured by HR) and a retention rate of 85% [40,43-45]. Participants’ weight and body composition will be measured weekly.

To ensure high compliance in session attendance, the instructor will hold weekly one-on-one meetings with participants to provide personalized feedback and encouragement. Participants’ HR data will also be reviewed during these meetings. Additionally, the study coordinator will remind participants of their scheduled sessions 1 day in advance through phone calls or texts. Attendance in sessions will be closely monitored, and records of attended exercise sessions will be maintained. Participants who miss sessions will be contacted via phone calls to encourage attendance.

Any adverse events occurring during or after HIIT sessions will be documented, with medical advice sought if necessary. Both intervention and control participants will receive instructions to maintain a eucaloric diet throughout the study. Dietary adherence will be monitored biweekly by a registered dietitian using the Automated Self-Administered 24-Hour Dietary Assessment Tool (National Cancer Institute) [36]. This tool will be administered via phone calls 3 times a week, covering 2 weekdays and 1 weekend day. Additionally, control participants will be instructed to refrain from engaging in intense physical activities during the study period. Physical activity adherence will be assessed biweekly using the short form of IPAQ, also administered via phone calls [32].

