### Study Feasibility

Table 2 shows the study feasibility metrics. Continuous data collection on feasibility parameters, such as response rate, screening yield, enrollment rate, time to enrollment, intervention compliance, resource use (cost and staff time), and retention rate, will be conducted throughout the study.

**Table 2 table2:** Study feasibility metrics.

Parameters	Calculations
Response rate	Number of individuals responded to the invitation/number of individuals invited
Screening yield	Number of individuals diagnosed with i-IFGa/number of individuals screened
Enrollment rate	Number of individuals enrolled/number of individuals diagnosed with i-IFG
Time to enrollment	Average time taken from sending the invitation to enrolling one participant in the trial
Intervention compliance	Number of HIITb sessions attended/Total number of HIIT sessions
Resource use	Program costs: Includes screening cost, cost of procedures, intervention cost, participant incentives, and other costs. Staff time: Time spent screening and recruiting participants, time spent delivering the intervention, time spent making phone calls to participants, time spent implementing the study procedures, and time spent on baseline and follow-up assessments.
Retention rate	Number of participants attended follow-up visits/number of participants enrolled

^a^i-IFG: isolated impaired fasting glucose.

^b^HIIT: high-intensity interval training.

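### Applied every week, the 5% step passes 100% of heart rate reserve in week 7, and the compliance metric scored on those targets mixes presence with intensity

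*Protocol article*

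**What the plan says.** All of the schedule is in the Intervention section of the protocol article.

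- Scale: "The target HR will be calculated using the Karvonen method".
- Start: "Exercise intensity will begin at 75% of the estimated maximum HR reserve (HRR").
- Step: it "will increase by 5% every week, as tolerated or deemed necessary by the instructor, over the 8-week intervention period". No ceiling and no week-by-week targets are printed.
- Tolerance: the goal is held by averaging rises and falls over the workout phase, "with a target to maintain within a 10% offset from the HRR goal". Whether the 10% is in points or relative is not stated.
- Sessions: groups meet "at specified times on Mondays, Wednesdays, and Fridays, spanning 8 weeks", with at most 24 sessions per person.
- Attendance: "Participants will need to adhere to within-session HR targets at an 80% rate (or greater) for a session to be counted as attended".
- Completer: "participants will need to attend 19 out of 24 sessions".

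Table 2 (Study Feasibility) defines intervention compliance as the number of HIIT "sessions attended/Total number of HIIT sessions". The Primary Outcomes section lists the feasibility metrics as primary.

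**The concern.** Two features of the printed plan interact. The escalation, followed as written, runs off the top of the scale on which it is expressed. The rule for counting a session as attended is tied to the heart rate targets that this escalation produces.

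At stake is the meaning of a primary feasibility result. A compliance figure that falls in the last weeks could mean that participants stopped coming. It could equally mean that they came and did not reach a target near or above their estimated maximum. These call for different decisions about the main trial that this study is meant to inform. The reported figure cannot separate them, and the same person can receive different figures depending on which target is used for scoring.

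**Working it through.** **Inputs**, all from the Intervention section: start 75% of reserve, step 5% per week, 8 weeks, 3 sessions per week, 10% offset, completer threshold 19 of 24.

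**Reproducing the plan's own figure.** 3 sessions × 8 weeks = 24, as printed. The completer threshold is 19/24 = 79.2%.

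**Scale.** Under Karvonen, target = resting rate + f × (maximum − resting), where f is the fraction of reserve. At f = 1 the target is the estimated maximum. At any f above 1 it exceeds the estimated maximum by (f − 1) × reserve.

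**Target in week w**, with week 1 at the starting value and one step at each later week:

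- additive reading: 75 + 5(w − 1)
- relative reading: 75 × 1.05^(w − 1)

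| Week | Additive target, % | Lower edge, 10 points | Lower edge, 10% relative | Relative target, % | Lower edge, 10 points | Lower edge, 10% relative |
|---|---|---|---|---|---|---|
| 1 | 75 | 65 | 67.5 | 75.0 | 65.0 | 67.5 |
| 5 | 95 | 85 | 85.5 | 91.2 | 81.2 | 82.1 |
| 6 | 100 | 90 | 90 | 95.7 | 85.7 | 86.1 |
| 7 | 105 | 95 | 94.5 | 100.5 | 90.5 | 90.5 |
| 8 | 110 | 100 | 99 | 105.5 | 95.5 | 95.0 |

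Both readings of 5% first exceed 100% in week 7. The offset brings the lower edge below 100% in weeks 6 and 7 on every reading. In week 8 the lower edge is 99 to 100% on the additive reading and about 95 to 95.5% on the relative reading. The target is an average over a workout that includes active rest, so an average of 99 to 100% implies intervals at or above the estimated maximum.

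**Effect on the counts**, for a person present at all 24 sessions who meets every target that is treated as attainable:

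| Scoring assumption | Credited sessions | Compliance | Reaches 19? |
|---|---|---|---|
| Against the adjusted target | 24 | 100% | yes |
| Nominal target, week 8 lost | 24 − 3 = 21 | 87.5% | yes |
| Nominal target, weeks 7 and 8 lost | 24 − 6 = 18 | 75.0% | no |

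The article does not state which row applies.

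**The case against.** The strongest reply is that the escalation is conditional. It applies as tolerated or as the instructor judges necessary, and the balance of rest and effort is adjusted to individual response. On that view 105% and 110% are the upper path of a titrated progression and not fixed targets. This stands, and for that reason the point is confined to the step being applied every week.

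A second reply is that the missing scoring rule may sit in the full protocol, since a journal article condenses. The natural reading of a within-session target is also the one set for that session, and the article reports 91% within-session adherence in the team's previous interventions. This has weight, and the silence alone would not be a finding. But the schedule, the scale and the definition of an attended session are all printed here. Scoring against the adjusted target also leaves the metric mixed: attendance would then depend on a target that an unblinded instructor may lower.

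A third reply is that requiring heart rate adherence for attendance is the authors' explicit choice. That is fair, and the measure can be kept. The same section, however, also uses attendance in the ordinary sense, with session records kept and calls made to those who miss sessions. Presence therefore deserves its own figure.

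A reader might go further and infer that no one could be a completer. The documents do not support this. It needs nominal scoring and the loss of both week 7 and week 8, while the week 7 lower edge is 90.5 to 95%. Counting week 6 as lost too (24 − 9 = 15) is weaker still, since its lower edge is at most 90%. The maximum is also an estimate, so some individuals may exceed it.

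A reader might also infer that completer status decides who enters the final analysis. The Statistical Analysis section (Objective 2) specifies intention-to-treat and models study group, and no listed outcome is restricted to completers.

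**Conclusion.** The point holds in a limited form. Applied every week, the printed step passes 100% of estimated reserve in week 7 and ends at 110% (additive) or 105.5% (relative), with no stated limit. This needs no outside assumption beyond taking week 1 as the starting value.

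The consequence for the results is conditional. The primary compliance metric and the completer label combine presence with intensity, and they could understate attendance in the last weeks. For one person present throughout, credited sessions range from 18 to 24 according to the scoring target and which late weeks can be met. Only the lowest value, which assumes nominal scoring and no credit in weeks 7 and 8, falls below 19.

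The printed schedule must be reconciled with its scale. Nothing here says what the intensity should be.

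**What to change.** 1. Reconcile the starting intensity, the weekly step and the 8-week length with the heart rate reserve scale, and say whether the 5% step and the 10% offset are in points or relative. Which element changes, and to what, is for the investigators.
2. State that each session is scored against the target actually set for that participant at that session, and record that target.
3. Report two figures by week and overall: presence at sessions, and heart rate target adherence among sessions at which the participant was present. Say which of them enters the compliance row of Table 2 and the completer label.

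The cost is a few sentences of protocol wording and one extra tabulated variable. Attendance records and chest-strap heart rate data are already kept, so no new measurement is needed. The session target must be logged where it is not already.

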### Sample Size Calculation

Assuming a Cohen *d* of 0.3 to <0.7 (medium standardized effect size) [25,59] for FPG in the planned main trial, with an alpha of 5% and a power of 90%, a sample size of 15 participants per treatment group is deemed necessary for this pilot study. Factoring in a 10% loss to follow-up in each group, the total sample size was estimated to be 34 participants (17 per group).

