### Statistical Analysis

#### Quantitative Research

##### Objective 1

Continuous variables will be summarized using either mean (SD) or median (IQR), depending on their distribution, which will be visually assessed through histograms. Categorical variables will be presented as counts (n) and percentages (%).

##### Objective 2

The analyses will adhere to the “intention-to-treat” principle. Between-group differences in changes in continuous variables from baseline to 8 weeks will be analyzed using mixed-effects linear regression models, while categorical variables will be assessed with log-binomial models. Skewed variables will be log-transformed prior to analysis. Fixed effects will include the study group (intervention vs control), timepoint (follow-up vs baseline), and the interaction between the study group and timepoint. Random effects will be specified for participants to account for the correlation between repeated measurements on the same individual. The *P* value for the study group-by-timepoint interaction will be used to evaluate the difference in changes between the study groups. The correlation between changes in fasting glucose levels and the indices from baseline to 8 weeks will be assessed using either Pearson or Spearman correlation coefficients, depending on the nature of the data distribution. Mixed-effects linear regression models will be used to compare CGM metrics between study groups, adjusting for baseline values. These models will also examine within-participant differences in CGM metrics between exercise and non-exercise days. Statistical significance will be considered with a 2-sided *P* value<.05 with no adjustments for the multiplicity of comparisons. All analyses will be conducted using Stata (version 18.0; StataCorp LLC).

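### The completer rule, which only the HIIT arm can fail, is not reconciled with intention to treat, and its definition of attendance blurs the primary compliance metric

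*Protocol article*

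**What the plan says.** Four statements in the protocol article bear on this point.

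- **Completer rule (Intervention).** "participants will need to attend 19 out of 24 sessions to be included as a “completer” in the final data analysis". The same sentence defines a countable session: "Participants will need to adhere to within-session HR targets at an 80% rate (or greater) for a session to be counted as attended". Controls have no sessions and no matching criterion.
- **Analysis principle (Statistical Analysis, Quantitative Research, Objective 2).** "The analyses will adhere to the “intention-to-treat” principle". The rest of that section describes the mixed models and names no completer, per-protocol or supplementary set.
- **Heart-rate target (Intervention).** "Exercise intensity will begin at 75% of the estimated maximum HR reserve (HRR) and will increase by 5% every week", as tolerated or as the instructor judges necessary, over 8 weeks. The aim is to stay within a 10% offset of the goal.
- **Medical clearance (Intervention).** "participants in the intervention group will be required to obtain medical clearance from their general practitioner before starting the HIIT sessions". Under Randomization and Blinding, "Participants will be equally randomized into either the intervention or control group after completing baseline assessments and being found eligible". Clearance is not among the eligibility criteria in screening steps 1 to 3 or in the footnote to Table 1.

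Table 2 (Study Feasibility) defines intervention compliance as HIIT sessions attended over total HIIT sessions. The feasibility metrics are primary outcomes. Between-group efficacy is secondary.

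**The concern.** Completer status is known only after allocation and can be failed in one arm only. The sentence that creates it links it to the final data analysis, while the section that governs that analysis promises intention to treat and does not mention completers. Two analysts could therefore follow this protocol and report different efficacy estimates: one from all 17 HIIT participants, the other from those who reached 19 sessions, each compared with all controls. If people who adhere better also improve more, the second estimate favours HIIT even when HIIT does nothing. The size of that estimate matters because the study is meant to inform the design of a larger trial.

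A primary outcome is also affected. A feasibility study needs to tell people who did not come from people who came but could not reach the prescribed intensity, because the remedies differ. With attendance defined by heart rate, the compliance ratio merges the two.

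**Working it through.** **The plan's own figures.** Sample Size Calculation gives 15 per group and 10% loss: 15/(1 − 0.10) = 16.7, so 17 per group and 34 in total. This reproduces, and nothing below changes it. The planning effect for fasting glucose is *d* 0.3 to below 0.7. The completer threshold is 19/24 = 79.2%.

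**How many could fail the rule.** The protocol does not say. If sessions are independent with a common chance of qualifying (an assumption), the binomial probability of at least 19 out of 24 is:

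| Chance that a session qualifies | 0.91 | 0.85 | 0.80 | 0.75 | 0.70 |
|---|---|---|---|---|---|
| P(completer) | 0.98 | 0.86 | 0.66 | 0.42 | 0.23 |

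The 0.91 borrows the within-session adherence reported from the team's earlier interventions, which is not quite the same quantity. The rule could remove almost nobody or most of the arm.

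**Bias if the rule governs inclusion.** Assume no true effect, change scores with SD 1, a latent adherence score correlated ρ with improvement, and a share *p* of the HIIT arm kept. The expected shift toward HIIT is ρ × φ(z)/*p*, where z is the (1 − *p*) quantile of the standard normal and φ its density.

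- *p* = 0.85: φ(z)/*p* = 0.274, so the shift is 0.2 × 0.274 = 0.055 to 0.5 × 0.274 = 0.137 SD.
- *p* = 0.75: φ(z)/*p* = 0.424, so the shift is 0.085 to 0.212 SD.
- *p* = 0.60: φ(z)/*p* = 0.644, so the shift is 0.129 to 0.322 SD.

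A simulation with 17 per arm and 40,000 runs per setting, using a t-test on change with only the HIIT arm restricted, agrees:

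| Completers (mean kept of 17) | Bias toward HIIT, ρ 0.2–0.5 | Two-sided type I error |
|---|---|---|
| 85% (14.5) | 0.06–0.14 SD | 0.051–0.065 |
| 75% (12.8) | 0.08–0.21 SD | 0.054–0.086 |
| 60% (10.2) | 0.13–0.32 SD | 0.061–0.123 |

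With ρ = 0 the bias is nil. With everyone kept, the rejection rate stays at about 0.05 in every setting.

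**Compliance metric.** Take one participant present at all 24 sessions who meets the heart-rate criterion in 18, and another present at 18 who meets it in all of them. Both score 18/24 = 75% and neither is a completer. The first has perfect attendance and the second missed a quarter of the programme. Elsewhere the protocol uses attendance in its ordinary sense: the Intervention section speaks of missed sessions, and Table 4 of an attendance log.

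**Heart-rate scale.** If every weekly step is applied, 75 + 5 × (week − 1) gives 75, 80, 85, 90, 95, 100, 105 and 110% of heart-rate reserve in weeks 1 to 8. Read as compounding growth, it gives 75 × 1.05⁶ = 100.5% in week 7 and 75 × 1.05⁷ = 105.5% in week 8. Either way the nominal target passes the top of its own scale, and this target feeds the attended and completer rules.

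**Clearance.** Randomisation follows eligibility, clearance is not an eligibility item, and only the intervention group needs it. On this text it falls after allocation. No section says how a participant without clearance is followed or counted.

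**The case against.** The best defence is that completer is a label. The protocol sets the word in quotation marks, no sentence says that non-completers are dropped, and the Objective 2 section, which directly governs the efficacy analysis, says intention to treat. Details of a supplementary set often sit in an analysis plan, which is not at hand. This stands in part. A reader might infer that the protocol excludes non-completers and so contradicts itself outright, but the text does not establish that. It leaves open two readings with different results, and it never chooses.

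The size can also be challenged. The completer shares and correlations are assumptions. At 85% completers the bias is under half the standard error of a 17 v 17 comparison (√(2/17) = 0.34 SD). That is fair, and it is why a range is given.

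Three further inferences are tempting and fail:

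- **Clearance as a filter that favours HIIT.** It is a condition for starting sessions. Under intention to treat, an uncleared participant stays in the HIIT arm untreated, which would tend to dilute the effect. Bias toward HIIT would need such people to be withdrawn or not followed, which the protocol does not say.
- **Distorted retention.** Table 2 counts attendance at follow-up visits over enrolment. Neither completer status nor heart rate enters it.
- **Only 18 sessions can count (weeks 1 to 6, at or below 100% of reserve), one short of 19.** Escalation is as tolerated, and the 10% offset puts the lower edge at about 95% for a nominal 105% and at 99–100% for 110%.

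On compliance, the definition is explicit and attendance and heart-rate data are both collected, so the metric is not contradictory. It still cannot answer the feasibility question on its own.

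**Conclusion.** The point holds as an unresolved conflict. A post-randomisation rule that only the HIIT arm can fail is linked to the final analysis and is not squared with the intention-to-treat statement. If it governs inclusion, the bias toward HIIT is about 0.06–0.32 SD under the assumed 60–85% completers and correlations of 0.2–0.5. At the upper end this is as large as the bottom of the planning range. It is zero if adherence is unrelated to improvement, or if completer is only a label. The compliance point needs no such assumption: it follows from the two definitions.

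The heart-rate escalation and the timing of clearance are passages for the sponsor to reconcile, and neither shows bias by itself. A reader might rank all this as a critical flaw. The documents do not support that, because efficacy is a secondary, preliminary objective. It should still be settled before outcome data are seen.

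**What to change.** 1. In the Objective 2 section, state that every between-group efficacy estimate includes all randomised participants in their allocated arm, regardless of attendance or clearance. In the Intervention section, limit completer to a labelled supplementary description of the HIIT arm.
2. In Table 2, report compliance as two numbers: sessions at which the participant was present, out of 24, and the share of those sessions that met the heart-rate criterion.
3. Ask the sponsor to reconcile the weekly escalation with the heart-rate reserve scale, and with the attended and completer rules that depend on it. Which intensity is right is for the sponsor.
4. Ask the sponsor to reconcile Randomization and Blinding with Intervention on when clearance falls relative to allocation, and to state that participants without clearance are followed and counted in the arm to which they were allocated.

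Items 1, 3 and 4 are wording. Item 2 uses attendance records and chest-strap data that are already collected, so its cost is one more line in the feasibility report. The sample size does not change.
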